### Treatment allocation

Eligible participants were randomly allocated to one of three groups A, B, & C (i.e. group A-sham, group B-treatment, and group C-control). The "QuickCalcs" program from the GraphPad Software [60] was used to randomly sequence 150 numbers (repeated 1×) into the three groups.

Each number and its randomised letter (A, B, or C) were placed in an opaque envelope. Each envelope was numbered consecutively from 1–150.

As each parent called to have their child screened they were allocated the next consecutive number once they were eligible, so that eligible participant no. 1 was allocated to envelope no. 1, etc. The screener was unaware of the sequence of group allocation at the time of screening, hence allocation was concealed at time of recruiting.

### Blinding

Participants were blinded as to which intervention group they were allocated to, in an attempt to control for the Hawthorne Effect. Parents and teachers were blinded to which intervention group the children were allocated to, in an attempt to minimize rater bias when completing rating scales i.e. CPRS-R:L and CTRS-R:L. The registered Psychologist and the Clinical Psychologist were blinded as to which group participants were allocated to, in order to minimize bias when scoring and interpreting the data from the CPRS-R:L and CTRS-R:L.

The NET practitioners were not blinded in this study as they needed to know which participants were receiving which intervention, i.e. treatment versus sham protocol. The parents of the control group were also aware that their children were in the control group awaiting treatment at the completion of the study.

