### Objectives

The objectives of this research are to:

1. To determine whether the addition of the Neuro Emotional Technique (a new biopsychosocial intervention), to an existing medical regimen can improve clinical outcomes (i.e. reduce inattention, hyperactivity and impulsivity) for children with medically diagnosed ADHD.

2. Furthermore, to determine the responses in the short term (i.e. one month) and medium term (seven months).

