## Methods

### Design

Ethics approved, registered, interdisciplinary, placebo controlled, double blind, randomized clinical trial.

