### Analysis

Demographic and baseline characteristics of participant variables will be compared between the three randomised groups using the Restricted Maximum Likelihood (REML) in GenStat 10^th ^Edition [69].

The primary analysis will compare outcomes for each primary and secondary outcome measure between the three groups (treatment, sham and control) using the Restricted Maximum Likelihood (REML) in GenStat 10^th ^Edition [69], to estimate treatment effect with 95% CI. REML is a method for fitting mixed linear models (the models for ANOVA being special cases) which can produce unbiased (or less biased) estimates of variance and covariance parameters. This is a relatively new and powerful technique that allows for data sets that are unbalanced, have missing values, have treatments with unequal variances and/or have correlated error terms [70].

An intention-to-treat (ITT) analysis will be undertaken of the one month and seven month data from the CPRS-R:L and CTRS-R:L for the participants who commenced the study but did not complete.

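### The trial is labelled double blind, but control-arm parents know the allocation when they rate their child, and the primary comparison still includes that arm without naming NET versus sham as the confirmatory contrast

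*Protocol article*

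**What the plan says.** - **Label.** The Design section calls the study a "placebo controlled, double blind, randomized clinical trial". The Abstract does the same.
- **Parents as blinded raters.** The Blinding section states: "Parents and teachers were blinded to which intervention group the children were allocated to, in an attempt to minimize rater bias when completing rating scales". That sentence makes no exception for any arm.
- **Exceptions.** The next paragraph says that NET practitioners were not blinded, and then: "The parents of the control group were also aware that their children were in the control group awaiting treatment". No exception is stated for teachers or for the children.
- **Contact.** Under Protocol, the sham and NET groups each have eight sessions in the first month and six more over the next six months. The control group continues its existing regimen and has no study sessions.
- **Outcomes.** Under Measures, the two primary outcomes are Conners' subscales collected on both the parent form (CPRS-R:L) and the teacher form (CTRS-R:L). Neither form is given precedence.
- **Comparison.** The Analysis section says that the primary analysis compares each outcome "between the three groups (treatment, sham and control") by REML, with 95% confidence intervals for the treatment effect. No pairwise contrast is singled out.
- **Objective.** Objective 1 asks whether adding NET "to an existing medical regimen can improve clinical outcomes".

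**The concern.** The parent scale is one of two sources for the primary outcomes, and the article's own reason for blinding parents is to keep bias out of it. In the control arm that protection is absent: the rater knows that the child is waiting for treatment. The other two arms are also seen 14 times. A difference between either contact arm and control can therefore contain expectation, disappointment at waiting and the effect of attention, as well as any effect of NET.

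The sham arm exists to separate these. NET versus sham has equal scheduled contact and, as stated, parents and teachers blinded to which of the two the child receives. A primary comparison across all three groups does not give that contrast any priority. A positive three-group result, or a positive NET-versus-control estimate, on the parent scale could then be read under the double-blind, placebo-controlled label although it came from the arm where parents were not blinded and no placebo was given.

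**Working it through.** **1. Who is blinded, by arm, as the Blinding section states it**

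| Role | Sham (A) | NET (B) | Control (C) |
|---|---|---|---|
| Parent (CPRS-R:L rater) | blinded | blinded | aware |
| Teacher (CTRS-R:L rater) | blinded | blinded | blinded (no exception stated) |
| Child | blinded | blinded | no exception stated |
| Psychologists scoring the scales | blinded | blinded | blinded |
| Practitioner | aware | aware | no study sessions |
| Study sessions | 8 + 6 = 14 | 8 + 6 = 14 | 0 |

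On the parent scale, NET versus sham is the only pair in which raters in both arms are blinded. On the teacher scale all three pairs are rater-blinded, but the two pairs with control still differ in contact (14 sessions against none).

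**2. Inputs for the illustration**

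- SD 6.7, N = 63 before and 93 after allowance for dropout (Sample size justification). The article's 93 reproduces as 63 × 1.4686 = 92.5, rounded up.
- Equal arms are assumed: 63/3 = 21 and 93/3 = 31 per arm.
- Significance level 0.05, taken as two-sided for pairwise tests.
- Assumed state of affairs: NET and sham have the same mean, and control parents' ratings are worse by *b* points only because they know the allocation. The article gives no value for *b*, so a range is shown.

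**3. Three-group test**

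With group means (0, 0, *b*), the squared deviations from the overall mean sum to (2/3)*b*². The noncentrality is λ = *n* × (2/3)*b*² / 6.7², and the chance of significance is P(F′(2, 3*n* − 3, λ) > F₀.₉₅).

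For *b* = 3 (3/6.7 = 0.45 SD):
- 21 per arm: λ = 21 × 6 / 44.89 = 2.81; critical F(2, 60) = 3.15; probability 29.0%.
- 31 per arm: λ = 31 × 6 / 44.89 = 4.14; critical F(2, 90) = 3.10; probability 41.6%.

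**4. NET versus control alone**

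Two-sided t test with pooled SD, noncentrality *b* / (6.7 × √(2/*n*)). For *b* = 3 and *n* = 21 this is 1.45, giving 29.8%.

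| *b* (points) | SD units | Three-group, 21/arm | NET vs control, 21/arm | Three-group, 31/arm | NET vs control, 31/arm |
|---|---|---|---|---|---|
| 0 | 0 | 5.0% | 5.0% | 5.0% | 5.0% |
| 1 | 0.15 | 7.3% | 7.6% | 8.5% | 9.0% |
| 2 | 0.30 | 15.0% | 15.8% | 20.5% | 21.4% |
| 3 | 0.45 | 29.0% | 29.8% | 41.6% | 41.5% |
| 4 | 0.60 | 48.2% | 47.8% | 66.4% | 64.3% |
| 5 | 0.75 | 68.2% | 66.3% | 85.7% | 82.8% |

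**5. NET versus sham**

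This contrast does not involve the control arm's mean. If parents in both contact arms stay blinded, its error rate stays at 5% whatever *b* is.

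**The case against.** **The article discloses the exception.** It does, in the Blinding section itself, and the sentence on parents can be read as covering NET against sham only. This is loose drafting and not concealment. It stands as far as it goes, but the label in the Abstract and Design is unqualified, and the disclosed exception is not carried into the Analysis section.

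**Naming a contrast is detail for an analysis plan.** This is the strongest objection. A condensed article need not set out a hierarchy of contrasts, and it does not say that an overall three-group test decides efficacy. What it does fix is which comparison is primary, and that comparison includes the arm whose parents are unblinded. The point rests on that statement, not on missing detail.

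**The shift sizes are invented.** They are assumptions. The table also uses simple tests at one time point as a stand-in for the planned mixed model. It shows how sensitive the comparison is and does not estimate the trial's actual error rate.

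A reader might be tempted to go further. The document does not support these readings:
- *That NET versus sham is the only rater-blinded contrast overall.* Teachers are stated as blinded in all arms, so this is true of the parent scale alone.
- *That the control group receives nothing.* It continues its existing regimen; what it lacks is study contact.
- *That control children knew their allocation.* Only their parents are named as aware.
- *That Objective 1 means NET versus control.* Both contact arms keep their existing regimen, so the wording fits NET versus sham equally well.

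**Conclusion.** The point holds. The double-blind label claims a property that the parent scale lacks in one of three arms, and the comparison declared primary includes that arm. With no NET-specific effect, a 3-point shift in control parents' ratings would make the three-group test significant in about 29% of trials at 21 per arm and 42% at 31 per arm, in place of 5%. Over shifts of 1 to 5 points the range is 7% to 68% at 21 per arm and 9% to 86% at 31 per arm. These figures assume SD 6.7, equal arms, NET equal to sham, and a shift whose size the article does not give.

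Two limits apply. The rater-bias part concerns parent ratings only. The contact part affects any comparison with control, including one based on teacher ratings: those are rater-blinded as stated, but they cannot separate NET from the effect of 14 visits.

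**What to change.** **Analysis section.** State which contrast is confirmatory, for example:

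> *The confirmatory contrast is NET versus sham. NET versus control and sham versus control are secondary. For these, parent ratings are reported as unblinded in the control arm, and teacher ratings are shown as the rater-blinded evidence. Neither separates NET from the effect of study contact.*

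**Abstract, Design and Blinding.** Replace the double-blind label with a description by role and arm: participants and teachers blinded as stated; parents blinded for NET versus sham only; control-group parents aware; practitioners unblinded.

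Objective 1 need not be reworded. The Recruitment section says the last participant completed in March 2008, while the Analysis section is still in the future tense. The choice of contrast should therefore be dated and recorded as made before outcomes are compared by group.

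**Cost.** Wording only: no arm, visit or measure changes. The downside is a more modest claim from the control-arm comparisons.

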### Sample size justification

Calculations for the sample size were set with a significance level of 0.05 and the power of 80%.

As there are no prior studies conducted in the area of chiropractic or NET for an ADHD cohort, for power analysis purposes a SD of 6.7 was adopted based on data from Shortt [61], yielding a sample size of 63. The value of 6.7 for power testing is supported by findings from a paper on the meta-analysis of RCTs in ADHD responses to atomoxetine using the CRS [62]. This study revealed an average SD score of 6.7, which is consistent with the SD found in the Shortt data [61]. In a meta-analysis of psychotherapy dropouts the mean attrition rate was 46.86% [63,64]. Based on this drop-out rate it was prudent to increase the sample size by this figure, increasing it from 63 to n = 93.

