**Design/methods:**

A placebo controlled, double blind randomised clinical trial was designed to assess the effectiveness of NET on a cohort of children with medically diagnosed ADHD.

Children aged 5–12 years who met the inclusion criteria were randomised to one of three groups. The control group continued on their existing medical regimen and the intervention and placebo groups had the addition of the NET and sham NET protocols added to their regimen respectively. These two groups attended a clinical facility twice a week for the first month and then once a month for six months.

The Conners' Parent and Teacher Rating Scales (CRS) were used at the start of the study to establish baseline data and then in one month and in seven months time, at the conclusion of the study. The primary outcome measures chosen were the Conners' ADHD Index and Conners' Global Index. The secondary outcome measures chosen were the DSM-IV: Inattentive, the DSM-IV:Hyperactive-Impulsive, and the DSM-IV:Total subscales from the Conners' Rating Scales, monitoring changes in inattention, hyperactivity and impulsivity.

Calculations for the sample size were set with a significance level of 0.05 and the power of 80%, yielding a sample size of 93.

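### The drop-out allowance multiplies 63 by 1.4686 instead of dividing by 0.5314, so at the article's own attrition rate 93 enrolled leaves about 49 completers and roughly 70% power, not 80%

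*Protocol article*

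**What the plan says.** The relevant statements are in the Protocol article, under Sample size justification and in the abstract.

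- Error rates: "Calculations for the sample size were set with a significance level of 0.05 and the power of 80" per cent.
- Variability: "for power analysis purposes a SD of 6.7 was adopted", and the calculation is reported as "yielding a sample size of 63".
- Attrition: "In a meta-analysis of psychotherapy dropouts the mean attrition rate was 46.86" per cent.
- Allowance for attrition: "it was prudent to increase the sample size by this figure, increasing it from 63 to n = 93".
- The abstract (Design/methods) gives the result without the intermediate step: "the power of 80%, yielding a sample size of 93".

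There are three arms (Treatment allocation: "Eligible participants were randomly allocated to one of three groups A, B, & C"). The article does not state the allocation ratio, the sidedness of the test, or the difference and contrast that 63 was meant to serve.

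**The concern.** An allowance for drop-out should leave the required number of children after the expected losses. The rate quoted is a proportion of those who start, so the losses apply to the 93 enrolled, not to the 63 needed. Increasing 63 by the attrition percentage therefore under-corrects, and the gap becomes large when the rate is close to one half.

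The power statement is at stake. Both the abstract and the sample size section attach 80% power to an enrolment of 93. If attrition occurs at the rate the authors chose, a calculation based on completers does not support that figure. A reader who relies on it would take a null result as stronger evidence against an effect than the design could give.

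**Working it through.** **Inputs.** From Sample size justification: required number 63, power 80%, significance level 0.05, attrition 46.86%, enrolled number 93. Assumed because the article does not say: equal arms (63 / 3 = 21 each), a two-sided test (one-sided also tried), and 63 as the total number of completers needed.

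**Step 1: reproduce the article's figure.** 63 × (1 + 0.4686) = 63 × 1.4686 = 92.52, rounded up to 93. This matches exactly, and it matches the wording, which says the size was increased by that percentage.

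**Step 2: the number needed to retain 63.** 63 / (1 − 0.4686) = 63 / 0.5314 = 118.55, rounded up to 119. Check: 119 × 0.5314 = 63.2. The shortfall in enrolment is 119 − 93 = 26.

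**Step 3: what 93 leaves at the stated rate.** 93 × 0.5314 = 49.42, or 16.5 per arm instead of 21. The shortfall in completers is 63 − 49 = 14.

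**Step 4: the attrition that 93 can absorb.** 1 − 63 / 93 = 0.3226, about 32%.

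**Step 5: power at 49.4 completers.** No target difference is needed. Take whatever effect gives 80% power at 63 and evaluate it at 49.42. In the normal approximation the expected test statistic is 1.960 + 0.842 = 2.802 at 63, and it scales with the square root of the sample size:

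2.802 × √(49.42 / 63) = 2.802 × 0.8857 = 2.481; power = Φ(2.481 − 1.960) = Φ(0.521) = 69.9%.

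Neither the standard deviation nor the difference enters. Other forms of the test give much the same answer:

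| Test | Power at 63 | Power at 49.4 |
|---|---|---|
| Pairwise, normal approximation, two-sided | 80% | 69.9% |
| Pairwise, noncentral t, two-sided | 80% | 69.3% (67.9% at 16 per arm, 70.7% at 17) |
| Three-group omnibus F | 80% | 68.4% (68.0% at exactly 49) |
| Pairwise, normal approximation, one-sided | 80% | 71.1% |

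The range is about 68 to 71%.

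**The case against.** The strongest objection is that 68 to 71% treats every child who drops out as contributing nothing. The Analysis section plans a REML mixed model, chosen partly because it tolerates missing values, and an intention-to-treat analysis of one-month and seven-month scores for children who did not finish. A child lost after the first month can still supply a one-month score. As an illustration, if half the attrition fell after month one, 93 × (1 − 0.2343) = 71 children would have one-month data, more than 63. This stands as a limit on the power figure. It does not rescue the calculation: the article claims no power gain from partial data, and its allowance for attrition only makes sense if drop-outs are counted as lost.

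It also stands that the treatment effect will be reported with a 95% confidence interval, which will show the precision actually achieved. That reduces the risk of misreading a null result but does not make the 80% statement correct.

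A reader might draw four stronger conclusions that the article does not support:

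- *That the trial has only about 69% power.* The figure is conditional on 46.86% attrition and on counting completers only.
- *That a particular target difference can be recovered.* With SD 6.7 and a two-sided test in the normal approximation, 63 would imply about 5.8 points if split over three arms, but about 4.7 if split over two groups. The article states neither. Leaving the target difference to the full protocol is ordinary condensation and is not part of this point.
- *That the 150 prepared envelopes cover the shortfall.* Under Treatment allocation they are a randomisation list, not an enrolment target. The stated target is 93.
- *That more children could be enrolled.* The Recruitment section says the last participant completed in March 2008.

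**Conclusion.** The inflation step is wrong, and this follows from the article's own figures. At 46.86% attrition the enrolment needed to retain 63 is 119, not 93, and 93 leaves about 49 completers. Nothing elsewhere in the article repairs this.

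The claim of 80% power at 93 therefore does not hold on the article's own premise. For the effect that gives 80% at 63, power is about 68 to 71%. That range assumes equal arms, 63 as the total number of completers required, and no contribution from children who drop out. It does not depend on the unstated target difference. The planned analysis may make the real loss smaller, mainly at one month. If attrition is no more than about 32%, 93 does retain 63 and the 80% stands.

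The error affects the power statement only. It introduces no bias and does not alter the outcomes or the analysis.

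**What to change.** Replace the claim of 80% power at 93 in both places, the abstract and Sample size justification, with a statement to this effect:

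> At 46.86% attrition, 93 enrolled children yield about 49 completers and roughly 70% power for the effect used to derive 63, if only completers are counted. Power of 80% holds only if attrition is at most about 32%. Retaining 63 completers at 46.86% attrition would have needed 119 enrolled.

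The authors may add that the mixed-model analysis can use partial data from children who drop out. No back-calculated target difference should be inserted, and no further enrolment is proposed.

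The cost is a sentence or two in two places and a less favourable power figure. Conduct, data and analysis are unchanged.

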### Recruitment

Recruitment for the study commenced in July 2006 and the first participant was enrolled in August 2006 and the last participant completed the study in March 2008. Each participant that qualified and was enrolled into the study and had their own start date, hence the staggered starts and as a result the study took 17 months to complete.

### Withdrawals

As part of the phone screening and the informed consent forms the parents of the participants were advised that they were free to withdraw their child/children from the study at any stage without any consequences.

### Protocol

Group A, the sham group, continued with their existing program and the sham protocol was added to their regimen. Group B, the treatment group, continued with their existing program and the NET protocol was added to their regimen. The participants in groups A and B attended a clinical facility for the first month and received eight treatments (two treatments per week) for approximately 15–20 minute sessions. Then, they were scheduled for another six treatments over the next six months (i.e. one treatment per month). Group C, the control group, consisted of children who continued with their existing ADHD treatment regimen as prescribed by their pediatrician, clinical psychologist and/or medical doctor.

### Neuro Emotional Technique (NET) protocol

#### Definition of NET

NET is a methodology of finding and removing Neuro Emotional Complexes (NECs). A NEC is defined as a subjective maladaptation syndrome adopted by the organism in response to a real or perceived threat to any aspect of its survival [40]. NET has been described as a treatment designed to address negative distressing stimuli, by removing these patterns by accessing the nervous system via stimulation of the spine.

Walker [40] described NET as a 15 step (Figure 1), multi-modal system that integrates the principles of several health modalities, including cognitive behavioural psychology principles, traditional Chinese pulse assessment, acupuncture theory and the feedback technique called muscle testing.

**Figure 1 F1:**
[figure not shown]
**15-step NET protocol**.

Muscle testing is non-invasive system of evaluating the function of the body [65]. NET protocol uses muscle testing throughout the procedure as an indicator for physiologic reactivity to a protocol of statements designed to challenge the cognitive recall of stimuli under contemplation [66].

NET is a system that evaluates structural, emotional, and chemical (i.e. toxic and nutritional) aspects of a patient's health and wellbeing using the manual muscle testing procedure as a diagnostic guide. Emphasis must be made that for the purpose of this study, the emotional aspects were the only issues addressed, investigating whether ones "emotional reality" affected one's mental wellbeing and behaviour patterns.

